#### Data Analysis

We will use descriptive statistics to summarize all patient- and provider-level outcomes and assess their relationship to patient engagement and activity data derived from the dDPP platform. All qualitative data collected via surveys will be analyzed using deductive and inductive (grounded theory) approaches, as described in phase 1. The results of quantitative and qualitative analyses in phase 2 will inform intervention approaches and assessments in phase 3.

### Phase 3: RCT

#### Study Design

In phase 3, we will conduct a two-arm pragmatic RCT to evaluate the impact of the engagement intervention tool plus the dDPP platform versus the dDPP platform alone on relevant prediabetes health outcomes and patient engagement in the dDPP.

#### Setting and Participants

The study trial will use a practice-level cluster-randomized design, with 1:1 randomization of 40 primary care practices resulting in 20 clinics per study arm. Randomization will be stratified by clinic size to ensure even distribution of different-sized clinics to the two study arms. The proposed sample size provides 80% power to detect a 30% increase in dDPP session completion and a 2 kg increase in 12-month weight loss in the intervention arm relative to the control. This calculation assumes 20% attrition, two-sided tests with a type I error rate of 0.05, and an intraclass correlation coefficient of 0.05.

We will recruit patients who meet the inclusion criteria with primary care providers at the study sites through the patient portal, an increasingly common and effective approach for recruitment [41-43], and through population-based outreach from NYULH prediabetes registries with assent from primary care providers. Intervention participation will last 12 months.

Patients enrolled in the intervention arm will receive access to the dDPP platform and the engagement system developed and refined in phases 1 and 2. Patients in the control arm will receive the dDPP alone. Providers in both arms will receive information on the study and educational material for their patients. Patients will receive enrollment and onboarding information and training for dDPP, the engagement system, and the home devices (weight scales and pedometers or fitness trackers), as outlined and refined in phase 2. In addition to the home devices, upon enrollment, patients will be provided a home A_1c_ testing kit and instructions for its use for the study.

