**Methods:**

This study will be conducted in 3 phases. In phase 1, we will use systematic UCD, Agile software development, and qualitative research methods to identify *key user* (patients, providers, clinical staff, digital health technologists, and content experts) requirements, constraints, and prioritization of high-impact features to design, develop, and refine a viable intervention prototype for the engagement system. In phase 2, we will conduct a single-arm feasibility pilot of the engagement system among patients with prediabetes and their primary care providers. In phase 3, we will conduct a 2-arm randomized controlled trial using the engagement system. Primary outcomes will be weight, BMI, and A_1c_ at 6 and 12 months. Secondary outcomes will be patient engagement (use and activity) in the dDPP. The mediator variables (self-efficacy, digital health literacy, and patient-provider relationship) will be measured.

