#### Data Analysis

All data will be descriptively summarized using frequencies and percentages for categorical variables and means and SDs for normally distributed data or median and IQR for skewed continuous variables. All available data will be included in data listings and tabulations with the number of missing values indicated. All analyses will follow the principle of intention-to-treat. Before analyzing the data, we will compare drop-out and missing data across study arms to assess whether any patient characteristics were associated with the missing data and, if necessary, perform additional analyses using multiple imputation methods.

The primary clinical outcomes (weight reduction or BMI, physical activity, and A_1c_) will first be analyzed as continuous variables using generalized estimating equation (GEE) models. Each GEE model will include a categorical indicator variable for the randomized study arm (control as reference), a variable corresponding to measurement time (baseline as reference), and an interaction term of the 2 variables. We will explore adjusting for any baseline demographics, use behavior, and survey responses that may be unbalanced between study arms. A Bonferroni-Holm correction method for multiple comparisons will be used to control the type I error rate of 0.05. A similar GEE model with a logit link function will be used to analyze the achievement of a 7% weight loss as a binary dependent variable.

We will also explore the extent to which engagement with the program acts as a mediator. We propose using a single mediator causal model approach with bootstrap-derived confidence intervals to measure the intervention’s effect on weight loss, physical activity, and A_1c_ through the specific mechanism of patient engagement.

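### The 80% power for a 2 kg weight difference is stated at two-sided 0.05 with no multiplicity allowance, but the analysis applies Bonferroni-Holm to several primary outcomes

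*Protocol article*

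**What the plan says.** All references are to the protocol article.

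- **Phase 3, Setting and Participants.** The design is a cluster trial with "1:1 randomization of 40 primary care practices resulting in 20 clinics per study arm". The power claim has two targets. The first is "The proposed sample size provides 80% power to detect a 30% increase in dDPP session completion" and the second is "a 2 kg increase in 12-month weight loss in the intervention arm relative to the control". The stated basis is "This calculation assumes 20% attrition, two-sided tests with a type I error rate of 0.05", together with "an intraclass correlation coefficient of 0.05". Multiplicity is not mentioned.
- **Phase 3, Data Analysis.** "The primary clinical outcomes (weight reduction or BMI, physical activity, and A_1c_) will first be analyzed as continuous variables". The same paragraph adds: "A Bonferroni-Holm correction method for multiple comparisons will be used to control the type I error rate of 0.05". It does not say which comparisons make up the family.
- **Abstract, Methods.** "Primary outcomes will be weight, BMI, and A_1c_ at 6 and 12 months". Engagement in the digital program is listed there as secondary.
- **Text after Table 1.** Change in body weight is the lead measure among the weight-based outcomes. It is not named as the only primary outcome or as the first one tested.

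**The concern.** Holm orders hypotheses by p-value, so no outcome has priority. With k hypotheses, the smallest p-value is compared with 0.05/k, the next with 0.05/(k-1), and so on. Twelve-month weight is compared with the full 0.05 only when every other hypothesis in the family has already been rejected. A power figure computed at 0.05 therefore describes an easier test than the one the analysis section prescribes.

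The other powered target points the same way. Session completion is an engagement measure and is not among the primary clinical outcomes in Data Analysis, so the power statement does not appear to have been built around the Holm family.

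What is at stake is interpretation. A non-significant weight result would be read as coming from a trial with 80% power for 2 kg, when power under the planned procedure could be clearly lower. Control of type I error is not in question.

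**Working it through.** **Inputs from the article.** Power 80%; two-sided 0.05; target difference 2 kg at 12 months; 40 practices, 20 per arm. Number of tests k: three outcomes in Data Analysis gives k = 3; three outcomes at two time points in the Abstract gives up to k = 6.

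**The plan's own figure.** The 80% can be neither rebuilt nor refuted, because patients per practice, total sample size and the SD of weight change are not given. It is taken as true at two-sided 0.05. The implied standardized effect is then

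1.9600 + 0.8416 = 2.8016,

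and Φ(2.8016 − 1.9600) = Φ(0.8416) = 80%, as stated.

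**Power at the first Holm step.** Power = Φ(2.8016 − z), where z is the two-sided critical value at 0.05/k.

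- k = 3: level 0.01667, z = 2.3940; Φ(0.4076) = 65.8%.
- k = 6: level 0.00833, z = 2.6383; Φ(0.1633) = 56.5%.

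With a noncentral t on 38 degrees of freedom (40 practices), calibrated to 80% at 0.05, the values are 64.5% and 54.2%. The normal approximation is therefore not exaggerating the loss.

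**Full Holm procedure.** The first-step value is a floor; power rises as other outcomes are rejected. Simulated power for weight (200,000 draws per setting, correlations 0 to 0.8):

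| Assumed power of each other outcome | k = 3 | k = 6 |
|---|---|---|
| No effect | 66% | 56–57% |
| 50% | 67–70% | 58–60% |
| 80% | 73–75% | 66–68% |
| 90% | 76–77% | 72–73% |
| Always rejected | 80% | 80% |

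The left-hand column is an assumption throughout; the article gives no power for the other clinical outcomes.

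**Detectable difference with 80% power at the first step.** Difference = 2 kg × (z + 0.8416) / 2.8016.

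- k = 3: 2 × 3.2356 / 2.8016 = 2.31 kg.
- k = 6: 2 × 3.4799 / 2.8016 = 2.48 kg.

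**The case against.** **The per-test level is inferred.** Data Analysis also uses a type I error rate of 0.05, there for the Holm-controlled rate. The power statement could have meant the familywise rate, with an adjusted level per test. This stands as a caveat. But the power statement lists its assumptions and includes no adjustment, so an unadjusted 0.05 is the natural reading, and if an adjusted level was used the text should say so.

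**The family is not defined, and detail of that kind is often left to an analysis plan.** This is fair for the listing itself. Holm might apply across outcomes, across time points, or both; a family of two would give a first-step power of 71%. The six-test count comes from the Abstract, which treats weight and BMI separately, whereas Data Analysis treats them as alternatives. The size of the loss is therefore uncertain. The mismatch between the two stated rules does not depend on it for any family of two or more.

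**Weight may have more than 80% power.** One sample size serves two targets, and the harder one normally sets it. If session completion was the binding target, the figures above are too low for weight. The article, however, states 80% for both.

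**Stronger readings a reader might infer.** One is that actual power is some definite figure, for example 57% to 74%. The documents do not support this: such a range needs an assumed family size and an assumed power for the other outcomes, and 74% is not a ceiling because Holm power can reach 80%. Another is that power must be judged for both targets jointly; the article sets no such requirement. A third is that unequal practice sizes lower power further by a known amount. Stratifying by clinic size shows that clinics differ, but the article gives neither the variation in enrolled numbers nor the SD needed to calculate an effect.

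**Conclusion.** The concern holds as a mismatch between the power statement and the analysis rule. It is not shown that the sponsor's calculation was itself wrong.

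The size is conditional on 0.05 having been the per-test level and on power there being exactly 80%. On those terms, power for the 2 kg effect lies between 66% and 80% for a family of three, and between about 57% and 80% for a family of six. The lower ends are 14 and 23 or 24 points below the stated figure (80 − 65.8 = 14.2; 80 − 56.5 = 23.5). The upper end is reached only if every other hypothesis in the family is rejected.

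**What to change.** Choose one of two routes before outcome data are seen by arm.

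1. **Make the test match the calculation.** Name 12-month weight change as the single primary comparison, tested at two-sided 0.05, and apply Holm to the remaining outcomes. If the 0.05 is meant to hold across all outcomes together, test the remaining ones only after weight is significant. The stated 80% then belongs to the planned test.
2. **Make the calculation match the test.** Keep several primary outcomes, list every comparison in the Holm family with its time point, and align the Abstract with Data Analysis. State the level used for the power calculation. Then give power for weight as a range from the first-step value (about 66% for three tests, about 57% for six) up to 80%, or restate the detectable difference at the first step (about 2.3 kg or 2.5 kg). The first-step value should not be printed alone as if it were the power.

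Neither route needs more patients. The first costs wording; the second costs a less favourable stated figure.

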#### Procedures and Data Collection

Eligible patients will be identified and enrolled as in phase 2, with applicable modifications as identified through phase 2 study design review and optimization.

The main health outcomes assessed in phase 3 are listed in Table 1 and correlate to health measures most commonly monitored in patients with prediabetes and goal outcome measures assessed by the dDPP.

**Table 1 table1:** Phase 3 study outcomes.

Construct and measure				Data source		Collected at (months)

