#### Procedures and Data Collection

Eligible patients will be identified through (1) the review of patient data in the EHR and (2) provider referrals. Eligible participants will be consented by a member of the research team. Consented patients will be enrolled in the commercial dDPP and receive the patient-facing engagement intervention developed in phase 1. Patients will receive information and training on both the national DPP and the intervention dDPP and will be guided through downloading and enrolling in the dDPP platform. Patients will also receive wireless connected step trackers and weight scales and will be instructed on how to connect their devices to their dDPP account and upload their health data. Eligible physicians whose patients have been enrolled in the study will be included in the study and will receive the provider-facing engagement intervention developed in phase 1.

Patients and providers will be asked to complete surveys at various points throughout the study.

Patient-level data include the following:

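### Phase 3 leaves provider referral and provider assent as ways into a practice-randomized trial, so providers who know their arm could influence who enrolls

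*Protocol article*

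**What the plan says.** All places are in the protocol article.

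- **Unit of randomization** (Phase 3: RCT, Setting and Participants): a "practice-level cluster-randomized design, with 1:1 randomization of 40 primary care practices resulting in 20 clinics per study arm".
- **Recruitment channels, first statement** (same section): "We will recruit patients who meet the inclusion criteria with primary care providers at the study sites through the patient portal", and also "through population-based outreach from NYULH prediabetes registries with assent from primary care providers". Provider referral is not named here.
- **Recruitment channels, second statement** (Phase 3: RCT, Procedures and Data Collection): "Eligible patients will be identified and enrolled as in phase 2". The rest of that sentence leaves room for changes arising from the phase 2 review, without naming any.
- **The route this points to** (Phase 2: Feasibility Pilot, Procedures and Data Collection): "Eligible patients will be identified through (1) the review of patient data in the EHR and (2) provider referrals".
- **What differs between arms** (Phase 3: RCT, Setting and Participants): "Patients enrolled in the intervention arm will receive access to the dDPP platform and the engagement system developed and refined in phases 1 and 2"; control patients receive the dDPP without that system. The Study Overview describes the engagement tool as having a provider-facing side as well as a patient-facing one. In phase 2, physicians receive it when their patients have been enrolled.
- **Handling of imbalance** (Phase 3: RCT, Data Analysis): intention-to-treat, GEE models with an arm-by-time interaction, and exploratory adjustment for baseline variables found to be unbalanced.

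**The concern.** Randomizing practices gives comparable groups of patients only if entry of patients within practices does not depend on the allocation. The text gives providers two points of influence: referral, carried in from phase 2 by cross-reference, and assent to registry outreach. Providers in intervention practices will know their arm once they use the tool. If they then refer or assent to a different kind of patient than control providers do, the arms differ in prognosis before treatment starts.

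The article itself makes motivation relevant to outcome. Under dDPP Platform: Noom it reports greater weight loss at 65 weeks in those who engaged more, and in-app engagement measures that predicted weight loss. Selective entry on motivation could therefore shift both quantities used for the sample size (session completion and 12-month weight loss), and also the planned mediation analysis through engagement.

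The planned analysis would not reliably undo this. The arm-by-time term removes a difference in starting weight, not one in expected trajectory. Intention-to-treat keeps the groups as enrolled, and enrollment is where the problem would arise. Adjustment reaches only what is measured.

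**Working it through.** **1. The text.** The two phase 3 statements can be laid side by side.

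| Route | Setting and Participants | Procedures (via phase 2) |
|---|---|---|
| Patient portal | yes | not named |
| Registry outreach with provider assent | yes | not named; overlaps with EHR review |
| EHR review | not named | yes |
| Provider referral | not named | yes, unless modified |

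Neither statement excludes the other's routes. Read together, referral is a phase 3 route unless an unnamed modification removes it.

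**2. The plan's own figure.** The article states 80% power for a 2 kg difference with 20 practices per arm, ICC 0.05, 20% attrition and two-sided 0.05. It gives no SD, patients per practice or total sample size, so the 80% can be neither reproduced nor contradicted. With a normal approximation, the individually randomized size per arm is n = 2 × (SD × (1.960 + 0.842) / 2)². Analyzed patients per practice, m, solve 20m / (1 + 0.05(m − 1)) = n, so m = 0.95n / (20 − 0.05n), then divided by 0.80 for attrition. For assumed SDs of 5, 6, 7 and 8 kg this gives about 8, 13, 22 and 41 enrolled per practice (320, 520, 880 and 1640 in total). The recruitment point does not depend on these numbers.

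**3. Standard error implied by the stated power.** SE = 2 / (1.960 + 0.842) = 0.714 kg.

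**4. Illustrative bias.** Let q be the share of an arm that enters selectively and d the difference in 12-month weight loss those patients would show on the dDPP anyway. Then bias = (q in intervention − q in control) × d, which is zero if selection is equal in both arms. Taking selection in one arm only and d = 2 kg, all assumed:

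- type I error = 1 − Φ(1.960 − bias/SE) + Φ(−1.960 − bias/SE)
- power for a true 2 kg effect, if the bias runs against the intervention = Φ((2 − bias)/SE − 1.960)

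| q | Bias | Type I error (nominal 5%) | Power if bias is adverse (nominal 80%) |
|---|---|---|---|
| 10% | 0.10 × 2 = 0.2 kg | 5.9% | 71% |
| 25% | 0.25 × 2 = 0.5 kg | 10.8% | 56% |
| 50% | 0.50 × 2 = 1.0 kg | 28.8% | 29% |

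Bias as a fraction of the 2 kg target equals q here only because d was set equal to the target.

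**The case against.** The strongest reply is that much of the mechanism rests on what a condensed article does not say.

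- **The two sections need not contradict each other.** The Procedures sentence allows modifications after phase 2, and the portal and registry channels may be those modifications, or the lists may be additive. This stands: a reader might infer a flat contradiction, and the text does not show one. It leaves open whether referral applies, and on the additive reading it does.
- **Timing and blinding are unstated.** The article does not say whether patients are identified before or after practices are allocated, and has no blinding statement. Such details are commonly left to the full protocol, so their absence is not itself a fault. This stands too. What remains is what the text does state: provider roles in entry, in a design where a provider-facing tool reveals the arm.
- **The tool reaches physicians only once patients are enrolled.** If the phase 2 procedure carries over, knowledge of the arm gained from the tool could affect only a provider's later patients. This narrows the mechanism but does not remove it.
- **Provider influence may be small and similar in both arms.** Assent attaches most clearly to registry outreach. In phase 2, research staff obtain consent. Providers in both arms receive study information, and patients in both arms receive the dDPP and home devices, so control providers also have reason to refer. One might infer that only intervention providers would refer, or that the bias must favor the intervention. The document supports neither, and intervention providers might equally refer harder cases.
- **Motivation is partly measured.** The phase 2 surveys, including engagement readiness and COM-B items, are carried to the phase 3 baseline subject to modification, and exploratory adjustment could use survey responses. That could reduce the bias, but adjustment chosen after imbalance is seen cannot reliably remove selection on unmeasured traits.

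**Conclusion.** The point holds as a risk that the plan's wording allows and could cheaply prevent. It is not a demonstrated bias. Provider referral carries into phase 3 by cross-reference unless an unspecified modification removes it, and provider assent is stated directly. Providers who know their arm could therefore influence entry, at least after the tool is in use.

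No size follows from the document. The 0.2 to 1.0 kg range assumes that 10% to 50% of one arm enters selectively, that the other arm has no such selection, and that the prognostic difference is 2 kg. No single value in that range should be read as an estimate, and the sign is unknown. Nor should the text be read as establishing that patients are recruited after allocation. The conclusion is conditional on providers knowing their arm at the time of referral or assent.

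**What to change.** Reconcile the two phase 3 sections so that they describe one arm-neutral route:

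1. Identify patients centrally, from the EHR and registry and through the portal, with the same invitation in both arms. Remove provider referral as an entry route.
2. Obtain provider assent on the central list before practice allocation is disclosed.
3. Where patients become eligible later, add them by the same central EHR query in both arms, and log assent refusals with reasons.
4. Report numbers identified, refused assent, invited and enrolled, by practice and arm.

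The means are largely in place: the ambulatory network shares one EHR, and the registry and portal are already planned channels. The cost is the loss of some referred patients. Those eligible through risk factors alone may not appear on a prediabetes registry, so the EHR query should be written to cover them. A list fixed before allocation also ages, because one eligibility criterion uses an A1c value from the last year; step 3 deals with this. Collecting assent early across 40 practices is modest extra work.

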**Clinical outcomes**						
	Weight reduction (kg)		Noom (via a wireless scale)		Baseline, 6, and 12	
	Physical activity (steps per day)		Noom (via a wireless pedometer)		Baseline, 6, and 12	
	A_1c_ (%)		A_1c_ home test kit		Baseline, 6, and 12	
